### Interim analyses {21b}

No anticipated problems that are detrimental to the participant were considered for interruption of this study.

### Methods for additional analyses (e.g. subgroup analyses) {20b}

We will use analysis of covariance (ANCOVA), as a supportive analysis, to compare differences between groups after the intervention, adjusting for values of the respective outcomes at baseline.

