### Outcomes {12}

The results will be evaluated at two time points: (1) baseline (before starting the intervention program) and (2) after 8 weeks of intervention. Trained assessors will conduct all assessments and reassessments. The evaluators will be physical therapists with at least 1 year of training experience in the evaluation instruments used in this study.

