### Sample size {14}

Based on the data from a previous study, performed by Mekki et al. [13] (*n*=45 participants, conducted in Tunisia), it will be necessary in a minimum sample size of 10 individuals per group and a total of 40 patients, considering the variable of mean lateral displacement of the pressure center mid-lateral displacement amplitude (COPml) in the follow-up of the intervention group, which performed NMES associated with PR program (±12.1 mm) and the control group that only performed standard PR (±7.2 mm). We also considered *p* value <0.05, power of 80% and loss of 20%.

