## Statistical methods

### Statistical methods for primary and secondary outcomes {20a}

The data will be analyzed using GraphPad Prism 5 (GraphPad Software Inc., San Diego, CA, USA). The normality of variables will be assessed by the Shapiro-Wilk test. The continuous variables with normal distribution and those with non-normal distribution will be presented as mean ± standard deviation (SD), 95% confidence interval (95% CI), and median (interquartile range), respectively, while categorical variables will be presented as absolute frequencies and percentages. Student’s *t* test for paired samples (parametric data) or Wilcoxon test (non-parametric data) will be used to compare the results before and after the intragroup intervention according to data distribution, and the effect size will be calculated using Cohen’s d. Comparison between groups will be performed using two-way analysis of variance (ANOVA) with repeated measures, followed by Bonferroni’s post hoc. Effect size was calculated using Cohen’s d. The significance level will be set at 5% (*p* <0.05).

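### Repeated-measures ANOVA, valid but usually less precise and with its deciding term unnamed, carries the between-group conclusion, while the planned baseline-adjusted ANCOVA is only supportive

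*Protocol article*

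**What the plan says.** Protocol article, Statistical methods for primary and secondary outcomes {20a}: "Comparison between groups will be performed using two-way analysis of variance (ANOVA) with repeated measures", with Bonferroni post hoc tests and a 5% significance level. The section does not name the term (group, time or group-by-time) that tests the treatment.

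Methods for additional analyses {20b}: "We will use analysis of covariance (ANCOVA), as a supportive analysis, to compare differences between groups after the intervention". The covariate in that model is each outcome's own baseline measurement. Baseline-adjusted ANCOVA is therefore prespecified but ranked below the ANOVA.

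Outcomes {12} gives two assessment occasions: "1) baseline (before starting the intervention program) and (2) after 8 weeks of intervention".

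Sample size {14} asks for a "minimum sample size of 10 individuals per group and a total of 40 patients", allowing for 20% loss. The allocation sections {16a} to {16c} describe no stratification or other balancing on baseline.

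**The concern.** With one value before and one after treatment, the named ANOVA can answer the between-group question in three ways.

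- **Group main effect.** It averages the baseline value, which treatment cannot have affected, with the 8-week value. The expected effect is halved.
- **Group-by-time term.** It is a one-way analysis of change scores, and each pairwise contrast is a difference in mean change. It subtracts the whole baseline value, where regression on baseline would subtract only the part that predicts follow-up.
- **Post hoc contrast of week-8 values only.** It makes no use of baseline.

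For a moderate correlation between baseline and follow-up, all three are less precise than the ANCOVA the protocol already plans. Precision is scarce with 8 to 10 patients per arm, and sizeable baseline differences between arms will arise by chance. The ranking means that the less precise result is the one on which the trial concludes.

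**Working it through.** **Inputs from the protocol.** Two time points; four arms, 1:1:1:1; 10 per arm; 20% loss, so 10 × (1 − 0.2) = 8 per arm; alpha 0.05 (two-sided assumed).

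**Assumed, because the protocol gives none.** Baseline-to-follow-up correlation r, taken from 0.3 to 0.95; equal variances at both times; true difference of 1 SD or 1.5 SD; for some runs alpha 0.05/6, since four arms give six pairs.

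**The plan's own figure.** The loss step is consistent: 8/(1 − 0.2) = 10 and 32/(1 − 0.2) = 40. The 8 cannot be reproduced or refuted, because the ±12.1 mm and ±7.2 mm are not labelled as means or SDs and the other quantity is absent. Nothing below depends on it.

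**Relative variance of a two-arm contrast (SD = 1 at each time).**

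- Week 8 only: 1
- Change score: 1 + 1 − 2r = 2(1 − r)
- ANCOVA: 1 − r²
- ANCOVA over change: (1 − r)(1 + r) / [2(1 − r)] = (1 + r)/2

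Estimating the slope multiplies the ANCOVA variance by about 1 + 1/(N − 6), which is 1 + 1/26 = 1.038 at N = 32 (8 per arm).

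| r | ANCOVA/change | Equivalent extra patients | Ratio with slope cost, 8 per arm | Equivalent extra patients |
|---|---|---|---|---|
| 0.5 | 0.75 | 1/0.75 = 33% more | 0.779 | 28% more |
| 0.7 | 0.85 | 18% more | 0.883 | 13% more |
| 0.8 | 0.90 | 11% more | 0.935 | 7% more |
| 0.9 | 0.95 | 5% more | 0.987 | 1% more |
| 0.95 | 0.975 | 3% more | 1.012 | about 1% fewer |

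Against week-8 values alone, before the slope cost, the gain is 1/(1 − r²): 33% more patients at r = 0.5 and 96% more at r = 0.7.

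**Simulated power** (four arms, pooled error, 20,000 runs per setting). One pairwise contrast, 10 per arm, difference 1 SD, alpha 0.05:

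| r | Group main effect | Week 8 only | Change (group-by-time) | ANCOVA |
|---|---|---|---|---|
| 0.3 | 27.1% | 58.5% | 45.3% | 61.3% |
| 0.5 | 24.0% | 58.5% | 58.9% | 70.1% |
| 0.7 | 22.4% | 58.5% | 80.4% | 85.2% |
| 0.8 | 20.6% | 58.6% | 93.1% | 94.6% |
| 0.9 | 20.0% | 57.8% | 99.8% | 99.9% |

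At 8 per arm, with the same effect and alpha, change against ANCOVA is 37.0% v 51.5% (r = 0.3), 48.6% v 59.3% (0.5), 70.6% v 75.7% (0.7), 85.9% v 88.0% (0.8) and 99.1% v 99.1% (0.9).

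At 8 per arm, difference 1.5 SD and alpha 0.05/6, the four analyses in table order give about 15, 56, 57 and 71% at r = 0.5, and 14, 57, 84 and 89% at r = 0.7. Change against ANCOVA is 96% v 97% at r = 0.8.

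With no true difference, every analysis rejected in about 5% of runs at alpha 0.05.

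**Chance baseline gap, any one pair of arms.** The SD of the difference is √(2/n): 0.50 SD at n = 8 and 0.447 SD at n = 10. The probability of a gap above 0.5 SD is P(|Z| > 1.00) = 32% at n = 8 and P(|Z| > 1.118) = 26% at n = 10.

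Given a gap g, the change-score contrast is off by −(1 − r)g and a week-8-only contrast by r·g. For g = 0.5 SD these are −0.25 and +0.25 SD at r = 0.5, and −0.15 and +0.35 SD at r = 0.7. ANCOVA removes the error in expectation.

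**The case against.** The strongest reply is that nothing here is invalid. Randomisation protects the planned ANOVA, type I error is about 5% for each term, and the adjusted result will be reported anyway. That stands: a reader might infer that the main analysis is biased or invalid, and neither the protocol nor the simulation supports this. The fault is one of precision and of error conditional on the baseline gap.

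A reader might also infer that the main analysis leaves baseline imbalance uncorrected. That is literally true only of a week-8-only contrast or the group main effect. The group-by-time term does subtract baseline, leaving −(1 − r)g, and the protocol does not say that either of the other two will be read. For the same reason, the very low power of the main effect is a risk of the unnamed term and not a forecast.

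Nor is the choice between ANOVA and ANCOVA left open, since the supportive label fixes precedence. Only the term within the ANOVA is unstated, and a full protocol or analysis plan may name it. The ranking, by contrast, is fixed in the article.

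The size is also fairly contested. Averaging three force-platform attempts may raise r, and above about 0.8 ANCOVA gains little over the group-by-time term; at 0.95 it loses slightly. Reassessment of all patients and multiple imputation aim to keep 10 per arm. These points limit the gain without reversing it at moderate r, and the table shows it at 10 per arm. Since r is unknown, ANCOVA is the safer choice: it gains most where change scores do badly and loses almost nothing where they do well.

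**Conclusion.** The concern holds as a matter of efficiency and of clarity about the deciding test. The main between-group analysis is valid, but the protocol ranks it above a planned analysis that is usually more precise and uses the same data.

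Against the group-by-time term, the gain is substantial at r of about 0.3 to 0.7, small at 0.8 and absent in power at 0.9. It is larger if a week-8-only contrast or the group main effect were read as the treatment test. These sizes rest on assumed values of r, effect size, equal variances and, for some runs, alpha. That ANCOVA allows for chance baseline gaps in proportion to r holds whatever r turns out to be.

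**What to change.** Make ANCOVA of the 8-week value on allocated group and baseline value the primary between-group analysis, reporting baseline-adjusted differences with 95% confidence intervals. Keep repeated-measures ANOVA as supportive, and state that only its group-by-time interaction is read as evidence on treatment. Section {20b} already plans the adjustment for each respective outcome, so the same order can apply to the secondary outcomes.

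No new data or model is needed, but the change is more than editorial. Trial status is given as completed, with recruitment to December 2022, so exchanging primary and supportive analyses could look data-driven. Section {16c} says the analyses will be blinded. If group codes are still closed, record the swap as a dated amendment through the route in section {25} (ethics committee and registry) before they are opened. If they have been opened, disclose it as a post hoc change and report both results.

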### Methods in analysis to handle protocol non-adherence and any statistical methods to handle missing data {20c}

Intention-to-treat analysis will be applied to include all randomized participants. Thus, the participants will be analyzed in the groups to which they will be allocated, even if they do not complete the intervention protocol (reassessments are intended for all patients). If this is not possible, the missing data will be handled using a multiple imputation method.

### Plans to give access to the full protocol, participant-level data, and statistical code {31c}

The datasets analyzed during the current study and statistical code are available from the corresponding author upon reasonable request, as is the full protocol.

## Oversight and monitoring

### Composition of the coordinating center and trial steering committee {5d}

The center is coordinated by [name] and the principal investigator, [name]. The trial will be directed by the investigators, [name] and [name]. No additional steering committees were considered for this study. All researchers will attend weekly meetings to discuss research progress and possible unforeseen events. There is no stakeholder and public Involvement Group (SPIG).

### Composition of the data monitoring committee, its role and reporting structure {21a}

Data monitoring committee is not considered as this is a low-risk intervention.

### Adverse event reporting and harms {22}

Adverse events (AEs) are not anticipated. The potential minor AEs that may be anticipated are fatigue, tachycardia, desaturation, dizziness, or blurred vision during the exercise that will be minimized by monitorization before and after the assessment and intervention. If the symptoms are persistent, the physiotherapist will stop exercise immediately and will conduct the first aid. The details of AEs will be reported in the case report form (CRF). All protocol violations and all AEs could be registered and reported in the final paper and serious AEs will be reported within 24 h to the Ethics Committee of the Federal University of Santa Maria.

### Frequency and plans for auditing trial conduct {23}

The trial will be continuously monitored by the principal investigators and discussed weekly in meetings with all researchers involved. As this study was unicentric and small, and the interventions were considered to be of low-risk, supervision by an independent data monitoring committee was not required. No additional audits were conducted in this study. However, the researchers were committed to reporting any adverse events that occurred during the study to the Ethics Committee of the Federal University of Santa Maria.

### Plans for communicating important protocol amendments to relevant parties (e.g. trial participants, ethical committees) {25}

Any changes to the study protocol will be submitted to the local Research Ethics Committee and modifications will be updated at ClinicalTrials.gov.

### Dissemination plans {31a}

The results of this study will be communicated to health authorities, health professionals, and the general public, at events and through publications in scientific journals as soon as the results are available. Additionally, each participant will receive a full report on the results of their assessments.

## Discussion

To our knowledge, this is the first study to investigate the effects of a short-term multimodal exercise program on postural balance and other outcomes with clinical significance in patients with COPD. Previous studies have demonstrated that deficits in postural balance are increasingly recognized as important secondary impairments in patients with COPD [6, 7, 10]. In addition, many risk factors that lead to impaired postural balance are common in elderly patients and systemic manifestations of COPD. Therefore, we suggest that most individuals with COPD are affected twofold [37]. However, the description of PR components in the ATS/ERS Pulmonary Rehabilitation Statement does not address the use of resources or strategies focused on improving postural balance [8, 9].

In this context, it is necessary to expand the focus of PR to include assessments and therapeutic strategies to improve balance, as proposed in this study. Considering that COPD is a complex inflammatory disease involving several types of inflammatory cells and multiple inflammatory mediators [38], novel PR models should provide a comprehensive understanding that incorporates the physiological and functional implications of different intervention strategies in a clinical setting. Nevertheless, the current evidence on the effects of multimodal exercise program on postural balance in patients with COPD is a significant gap in the literature.

Based on the recent recommendations from the official ATS workshop report international guidelines, a new approach to the future of PR is required [38]. Consistent with these recommendations and to ensure the principle of personalized rehabilitation, a combination of interventions that include the use of IMT and NMES may be particularly relevant. Janssens et al. (2013) were pioneers in encouraging further studies to determine the effects of IMT on postural balance in patients with COPD [39]. Recently, a randomized controlled trial demonstrated that IMT combined with endurance training enhanced inspiratory muscle function and balance in these patients [12]. Additionally, NMES was able to reduce DNA damage in patients with chronic kidney failure [14] and added to PR improve static postural balance in patients with COPD [13]. In this sense, the results of this study will reveal relevant clinical information regarding the adoption of new PR models through a multimodal exercise program. These results can also be applied to clinical practice in the field of physical therapy.

Our study has both strengths and limitations. Strengths include the adoption of a multimodal exercise program because this strategy may promote additional benefits on clinically relevant outcomes; use of the protocol for short-term intervention; inclusion of laboratory biomarkers for inflammatory profile, endothelial function, oxidative stress, and DNA damage that had not been reported in previous studies comparing therapeutic strategies in COPD patients [40]. Moreover, we will implement a combination of strategy modalities considered to be low-cost and feasible. One limitation is that the study will be performed at a single center, and it is not possible to include multiple centers because of the type of intervention and inability to blind the therapist to the treatment allocation.

The results from will reveal relevant clinical information about the adoption of new PR models through multimodal exercise program. Thus allowing to expand the focus of PR to include the assessment and balance deficits training in COPD. Physical therapists will be able to transfer this knowledge in clinical practice to improve the treatment of these patients.

## Trial status

Completed

ClinicalTrials.gov NCT04387318. The protocol version is number 3.0, dated May, 28, 2023.

The first patient was recruited on August 01, 2021; the recruitment will be completed on December 20, 2022.

## Data Availability

The datasets generated during and/or analyzed during the current study will be made available with other researchers on duly justified request. The authors [name], [name], [name] and [name] will have access to the final test data set.

## Abbreviations

ABC: Activities-specific Balance Confidence Scale
AE: 95% ellipse area
ANCOVA: Covariance
ANOVA: Two-way analysis of variance
ATS: American Thoracic Society
BESTest: Balance Evaluation Systems Test
CRF: Case report form
CONSORT: Consolidated Standards of Reporting Trials
COP: Center of pressure
COPap: COP anteroposterior displacement amplitude
COPD: Chronic obstructive pulmonary disease
COPml: COP mid-lateral displacement amplitude
COPvel: COP displacement velocity
ERS: European Respiratory Society
FES-I-Brazil: Falls Efficacy Scale-International-Brazil
HRQoL: Health-related quality of life
hsCRP: High-sensitivity C-reactive protein
IMT: Inspiratory muscle training
MEP: Maximal expiratory pressure
MIP: Maximal inspiratory pressure
NMES: Neuromuscular electrical stimulation
95% CI: 95% confidence interval
PR: Pulmonary rehabilitation
6MWT: Six-minute walk test
SD: Standard deviation
30-STST: 30-s sit-to-stand test
TUG: Timed Up and Go
1RM: One-repetition maximum
